**Fig. 1 Fig1:**
[figure not shown]
Study design

### Population

A total of 300 trauma patients will be included in the study. Both operatively and non-operatively treated patients will be included, irrespective of whether or not they were admitted to the hospital. In order to be eligible for inclusion, trauma patients have to meet the following inclusion criteria: having at least one traumatic fracture, being aged >18 years, and being able to fill out online questionnaires. In both the intervention- and control group, the duration between the patients’ actual trauma and their first consultation at the outpatient clinic for trauma patients can vary, depending on the treatment that was selected at the emergency department (i.e. admitted to hospital or sent home). Patients will be excluded if they have red flags (i.e. traumatic brain injury, pathological fractures, and/or cognitive limitations), if they do not speak Dutch, if their rehabilitation process takes place in a tertiary care facility, and/or when patients live outside the catchment area of the VUmc.

### Recruitment

#### Control group

Control group patients will be identified from hospital records. All eligible patients will be contacted by phone by one of the investigators. At this point, patients receive further information about the study, and in- and exclusion criteria will be verified by the coordinating investigator. Patients who are willing to participate and eligible will then receive an email containing a link to an online questionnaire. Clicking the link to the online questionnaire will serve as informed consent. Patients who do not respond within 1 week will receive a reminder email which will be resent after another week of not responding. If the patient does not reply to both emails one of the coordinating investigators will contact the patient by phone to inquire whether the patient is still interested and willing to participate as indicated earlier.

#### Intervention group

Intervention group patients will be identified during their first consultation at the outpatient clinic for trauma patients. During this consultation, patients will be informed about the study purpose and procedures by one of the investigators. Also, in- and exclusion criteria will be verified. Patients who are willing to participate and are eligible will receive an email containing a link to an online questionnaire. Clicking the link to the online questionnaire will serve as informed consent. Subsequently, patients will be prospectively followed and will receive additional online questionnaires at 3, 6 and 9 months follow-up. Patients who do not respond within 1 week to one of the aforementioned online questionnaires will receive a reminder email which will be resent after another week of non-responding. If the patient does not reply to both emails one of the coordinating investigators will contact the patient by phone to inquire whether the patient is still interested and willing to participate.

### Intervention conditions

#### Regular care

Patients in the control group received regular care (i.e. trauma care that was provided at the VUmc prior to implementation of the TTCM). During regular care, the trauma surgeon acts as the chief consultant and performs the post-clinical consultations, unaccompanied by professionals of other disciplines. Based on personal judgement, the trauma surgeon decides if and when physical therapy in primary care is needed. After referral to a physical therapist, patients select a primary care physical therapist themselves, usually in their residential area. Moreover, during a patients’ treatment by a primary care physical therapist, there is typically no regular contact between the surgeon and the primary care physical therapist.

#### The transmural trauma care model (TTCM)

Patients in the intervention group will receive care according to the TTCM at the outpatient clinic for trauma patients at the VUmc. Pre- and in-hospital trauma care remains unchanged and is equal to that provided to the control group. The essence of the TTCM is a regular feedback loop, in which the hospital team guides the primary care team by individual goal setting for each patient (see Fig. 2 for a schematic representation of the TTCM). The TTCM consists of four main components and will be explained below:

**Fig. 2 Fig2:**
[figure not shown]
Schematic representation of the TTCM

*Intake and follow up consultations by a multidisciplinary team consisting of a trauma surgeon and a highly specialized hospital based trauma physical therapist.* The trauma surgeon acts as the chief consultant and is responsible for assessing the bone- and wound healing process and additional medical procedures, such as the prescription of medication and indicating surgery. The hospital based physical therapist, on the other hand, assesses physical function (e.g. mobility, strength, walking pattern). The trauma surgeon and hospital based physical therapist indicate -as a team- if and when physical therapy in primary care is needed.
*Coordination and individual goal setting for each patient by the multidisciplinary hospital team.* This hospital team coordinates the patients’ rehabilitation process. The hospital based trauma physical therapist acts as case manager and repeatedly sets individual goals with the patient during the rehabilitation period.
*Primary care physical therapy by specifically trained trauma physical therapists organized in a network.*
This innovative “VUmc trauma rehabilitation network” consists of 40 physical therapists covering the region of Amsterdam. Patients in the intervention group with an indication for physical therapy treatment in primary care will be referred to one of the specialized trauma physical therapists of the VUmc trauma rehabilitation network. Prior to the implementation of TTCM, all 40 network physical therapists will follow a two-day training course led by trauma surgeons and hospital physical therapists. The course covers topics such as fracture healing, fracture treatment, complications and the most important principles of trauma rehabilitation. In addition, written working agreements will be discussed during the training course to assure optimal communication and use of IT services.
*E-health support for transmural communication (between hospital based trauma physical therapist and primary care based physical therapist) and treatment according to protocols.*

For the purpose of the TTCM, an existing electronic patient record is adapted and ten rehabilitation protocols have been developed for the most common fractures (e.g. hip, tibia, ankle, proximal humerus, vertebra), which will function as guidelines for the primary care trauma physical therapists. The protocols are linked to a secured email device through which hospital physical therapist and the primary care physical therapist will communicate repeatedly throughout the whole rehabilitation process.

### Outcome assessment

An overview of all outcome measurements is provided in Table 1.

**Table 1 Tab1:** Overview of all outcome measurements

Outcome	Measurement Instrument	Short term	Items	Itemscore	Interpretation
General ﻿HR-QOL	EQ-5D	EQ-5D	5	1–3	higher score: better health
Pain	Numeric Pain Rating Scale	NPRS	1	0–10	higher score: more pain
Perceived recovery	Global Perceived Effect	GPE	2	1–7	higher score: less recovery
Functional status	Patient Specific Function Scale	PSFS	3	100 mm VAS	higher score: less function
Patient satisfaction	Numeric Rating Scale	NRS	5	0–10	higher score: more satisfaction
Disease specific HR-QOL (upper extremity)	Quick Dash score	Q-DASH	11	1–5	sumscore 0–100, higher score: less function
Disease specific HR-QOL (lower extremity)	Lower Extremity Functional Scale	LEFS	20	0–4	sumscore 0–80, higher score: better function
Disease specific HR-QOL (vertebral fractures)	Roland Morris Disability Score	RMDS	24	yes/no	sumscore 0–24, higher score: more disability
Disease specific HR-QOL (multi trauma patients)	Groningen Activity Restriction Scale	GARS	18	1–4	sumscore 18–72, higher score: more restrictions
Healthcare utilization	Retrospective Cost Questionnaires				costs in Euro’s
Absenteeism	PROductivity and DISease Questionnaire	PRODISQ	1		total number of sick leave days
Presenteeism	WHO Health and Work Performance Questionnaire (NRS)	WHO-HPQ	1	0–10	higher score: better performance at work
Unpaid productivity loss			1		hours per week unable to perform unpaid activities

#### Baseline characteristics

At baseline, various demographic and trauma-related characteristics will be collected for all patients in the control- and intervention group, including age (years), gender (male/female), level of education (low/middle/high), medical history (none/chronic illness/musculoskeletal disease), type of trauma (traffic/fall/sport), injuries (upper extremity fracture/lower extremity fracture/vertebral fracture/multi trauma), treatment (operatively/conservatively), length of stay (days), and the well validated Injury Severity Score (ISS), used to provide an overall injury severity score for trauma patients [19]. The ISS score takes values from 0 to 75, and patients with an ISS > 16 are defined as multi-trauma patients. In the current study multi trauma patients are defined as having an ISS > 16 and/or having at least fractures in two or more extremities. Baseline characteristics will be collected using online questionnaires as well as data derived from electronic patient records.

#### Primary outcome measure

The primary outcome measure is general HR-QOL, measured using the Dutch version of the EQ-5D [20]. The EQ-5D consists of five questions representing five dimensions; mobility, self-care, usual activities, pain/discomfort and anxiety/depression. Each question is scored on a 3 point scale (1–3) with higher scores indicating greater severity level, resulting in a 5 digit index representing one of the 243 health status of the EQ-5D. Using the Dutch tariff, the participants’ EQ-5D health status will be converted into a utility score ranging from 0 (dead) to 1 (healthy). Additionally, quality adjusted life years (QALYs) will be calculated using linear interpolation between measurement points. The EQ-5D shows good psychometric properties in trauma patients with one or more fractures [21–23].

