**Methods:**

Patients will be recruited from the outpatient clinic for trauma patients of the VU University Medical Center (VUmc) if they have at least one fracture and were discharged home. A *controlled-before-and-after* study design will be used to compare the TTCM with regular care. Measurements will take place after the first outpatient clinical visit and after 3, 6 and 9 months. Prior to the implementation of the TTCM, 200 patients (50 patients per time point) will be included in the control group. After implementation 100 patients will be included in the intervention group and prospectively followed. Between-group comparisons will be made separately for each time point. In addition, the recovery pattern of patients in the intervention group will be studied using longitudinal data analysis methods. Effectiveness will be evaluated in terms of health-related quality of life (HR-QOL), pain, functional status, patient satisfaction, and perceived recovery. Cost-effectiveness will be assessed from a societal perspective, meaning that all costs related to the TTCM will be taken into account including intervention, health care, absenteeism, presenteeism and unpaid productivity. Additionally, a process evaluation will be performed to explore the extent to which the TTCM was implemented as intended, and to identify possible facilitators and barriers associated with its implementation.

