## Methods

### Design

To answer the research questions, a modified *controlled-before-and-after* study will be conducted at the outpatient clinic for trauma patients of the VU University Medical Center (VUmc), Amsterdam, the Netherlands. The modification of the original study design -in which both control group and intervention group are observed prospectively- is that in our design only the intervention group will be prospectively followed. This modification is required due to the limited resources available. Prior to the implementation of the TTCM, data of 200 control patients who received care as usual will be collected during an inclusion period of 4 months. The control group will consist of 4 clusters of patients who either had their first consultation at the outpatient clinic for trauma patients of the VUmc 0 (i.e. baseline), 3, 6 or 9 months ago. Per cluster, we aim to include approximately 50 patients, all of whom will be asked to fill out an online questionnaire once after providing informed consent. After implementing the TTCM, patients who enter the outpatient clinic for trauma patients of the VUmc and meet the inclusion criteria will be asked to participate in the intervention group of the study. Patients in the intervention group will be prospectively followed for 9 months (*n* = 100) and will be asked to fill out online questionnaires at baseline, 3, 6 and 9 months after their first consultation at the outpatient clinic for trauma patients. See Fig. 1 for a detailed illustration of the study design.

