#### Handling missing data

Missing data are assumed to be at random and will be imputed using Fully Conditional Specification and Predictive Mean Matching [45]. An imputation model will be constructed, including variables related to the “missingness” of data, variables that predict the outcomes, and all available midpoint and follow-up cost and effect measure values. The number of imputed data sets will be determined based on the number of participants with complete cost and effect measure values [46]. All of the imputed datasets will be analysed separately as specified below. Pooled estimates were subsequently calculated using Rubin’s rules [46].

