#### Economic evaluation

The economic evaluation will be performed from the societal perspective, meaning that all costs and consequences related to the intervention will be taken into account, irrespective of who pays or benefits. The mean difference in total costs between the intervention and control group will be compared to the corresponding mean difference in effects. For this, cost and effect differences will be estimated using seemingly unrelated regression analyses in order to correct for their possible correlation. To deal with the highly skewed nature of cost data, 95%CIs around the differences in costs will be estimated using the Bias Corrected and Accelerated Bootstrap method, with 5000 replications. Incremental Cost Effectiveness Ratios (ICERs) will be calculated by dividing the differences in costs by those in effects. To graphically illustrate the uncertainty surrounding the ICERs, bootstrapped incremental cost-effect pairs will be plotted on cost-effectiveness planes [47]. A summary measure of the joint uncertainty of costs and effects will be presented using cost-effectiveness acceptability curves, indicating the probability of an intervention being cost-effective in comparison with the control condition for a range of willingness-to-pay values (i.e. the maximum amount of money decision-makers are willing to pay per unit of effect gained) [48]. To test the robustness of the results, various sensitivity analyses will be performed [49]. All of the economic evaluation analyses will be performed in STATA, using a level of significance of *p* < 0.05.

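### Controls are measured once, so individual interpolated QALYs, and hence the patient-level cost-QALY regression, cannot be computed for the control group

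*Protocol article*

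**What the plan says.** Under Design: "The control group will consist of 4 clusters of patients", defined by time since first consultation (0, 3, 6 or 9 months). The target size of each cluster is about 50. On how often these controls are measured, the same section has "all of whom will be asked to fill out an online questionnaire once after providing informed consent". The 100 intervention patients complete four questionnaires each, at 0, 3, 6 and 9 months.

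Under Primary outcome measure, EQ-5D answers become utilities and, in addition, "quality adjusted life years (QALYs) will be calculated using linear interpolation between measurement points". No separate rule is given for controls.

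Under Economic evaluation, "cost and effect differences will be estimated using seemingly unrelated regression analyses in order to correct for their possible correlation". Bootstrapped cost-effect pairs then feed the cost-effectiveness plane and the acceptability curves. Again nothing is adapted for controls.

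Under Costs, by contrast, the recall period is adapted. Controls in the 9-month cluster recall 9 months, so one questionnaire gives them a full-period cost.

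Under Handling missing data, the imputation model is to include "all available midpoint and follow-up cost and effect measure values".

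**The concern.** Interpolating a QALY for a patient needs at least two utilities from that patient. Seemingly unrelated regression needs a cost and an effect on the same patient. With one questionnaire per control, the first condition fails for every control, and so the second fails whenever the effect is a QALY.

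The article gives the cost side a control-specific rule but gives the QALY side none. Cost-effectiveness is the stated aim of the study and its second research question. Without a stated rule, whoever analyses the data would have to devise the control QALY and its uncertainty after the data are in. One way of filling the gap would be to let the imputation model create the three visits that each control was never scheduled for. That would look routine but would rest on information the control group does not contain.

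**Working it through.** **Inputs from the protocol article**
- Control clusters: 4, about 50 patients each, one questionnaire per patient (Design).
- Intervention group: 100 patients, four questionnaires each (Design).
- Control cost recall: 3, 3, 6 and 9 months for the 0-, 3-, 6- and 9-month clusters (Costs).

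**Inputs assumed, because the article gives no figure**
- EQ-5D standard deviation σ: 0.20 to 0.30, equal at all time points.
- Within-patient correlation ρ in the intervention group: 0.3 to 0.7, the same for every pair of time points.

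**Step 1: reproduce the stated sizes.** 4 × 50 = 200 controls, as in the abstract ("200 patients (50 patients per time point) will be included in the control group"). 200 + 100 = 300, as under Population ("A total of 300 trauma patients will be included in the study").

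**Step 2: count what is jointly observed in controls.** Each time point has 50 controls. Each pair of different time points has 0. So:
- controls with two or more utilities: 0 of 200;
- controls with a cost-QALY pair: 0 of 200;
- controls with a 9-month cost and a 9-month effect on the same questionnaire: about 50.

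**Step 3: what imputing unscheduled visits would involve.** A complete control record would have 200 × 4 = 800 EQ-5D cells. The design supplies 200. The other 600 (600/800 = 75%) would be imputed. No control supplies a correlation between time points, so it would come from the intervention group or from the structure of the model.

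**Step 4: what the data can support.** The trapezium rule over 0.75 year gives weights 0.125, 0.25, 0.25 and 0.125, which sum to 0.75. The group-level control QALY is

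Q_control = 0.125·m0 + 0.25·m3 + 0.25·m6 + 0.125·m9,

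where m0 to m9 are the four cluster means. The clusters are different patients, so their means are independent and no within-patient correlation is needed.

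- Sum of squared weights: 2 × 0.015625 + 2 × 0.0625 = 0.15625.
- SE of control QALY: σ·√(0.15625/50) = 0.0559σ, that is 0.0112, 0.0140 and 0.0168 for σ = 0.20, 0.25 and 0.30.
- Variance of one intervention patient's QALY: σ²[0.15625 + ρ(0.5625 − 0.15625)], where 0.5625 = 0.75². The bracket is 0.2781, 0.3594 and 0.4406 for ρ = 0.3, 0.5 and 0.7.
- SE of intervention mean QALY: σ·√(bracket/100) = 0.0527σ, 0.0599σ and 0.0664σ.
- SE of the difference: the square root of the sum of the two squared standard errors.

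| σ | ρ = 0.3 | ρ = 0.5 | ρ = 0.7 |
|---|---|---|---|
| 0.20 | 0.0154 | 0.0164 | 0.0174 |
| 0.25 | 0.0192 | 0.0205 | 0.0217 |
| 0.30 | 0.0231 | 0.0246 | 0.0260 |

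These figures are before confounder adjustment and before any loss to follow-up.

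**The case against.** The strongest reply is that the sentence on interpolation does not say that it is done within each patient. Interpolating between the four control cluster means would satisfy it. That is fair, and it is the route recommended below. But it leaves the control group with one QALY estimate and no control QALY rows for the regression, so the Economic evaluation section must change on either reading.

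A second reply is that an article leaves detail to the full protocol or analysis plan. That would cover a missing formula. Here the article names the QALY method and the estimator, and the two do not fit the design it also describes.

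Three stronger readings are tempting, and the document does not support them.
- A reader might infer that no patient-level cost-effect regression is possible in controls. The 9-month cluster has 9-month recalled costs and 9-month utility, pain, recovery, function and satisfaction on the same patients. Regression and cost-effectiveness ratios for those effects can be fitted, openly, with about 50 against 100.
- A reader might infer that the imputation plan is itself wrong. The article speaks of missing data and does not say that unscheduled visits will be imputed. The 75% figure describes what would happen if they were.
- A reader might infer that the control QALY is essentially unknowable, because an individual's QALY standard deviation could lie anywhere from 0.40σ (ρ = 0) to 0.75σ (ρ = 1). Those correlations are limits, and the range describes the spread between individuals. The mean, on which the economic result depends, is identified.

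It is also true that the Economic evaluation section never names the QALY as its effect, and that the primary outcome is EQ-5D utility compared at each time point. Those comparisons are unaffected.

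**Conclusion.** The point holds for QALYs. None of the 200 controls can have an individual interpolated QALY, so the patient-level cost-QALY regression, and the bootstrapped cost-QALY pairs, plane and acceptability curve that follow from it, cannot be obtained for the control group as written. This follows from the design alone and needs no assumption. That the economic evaluation is meant to include a cost per QALY is an inference from the QALY being defined at all, though a natural one.

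The defect lies in the written route and not in the data. A mean QALY difference can be estimated at group level, with a standard error of about 0.015 to 0.026 QALY. That range rests on the assumed standard deviations, equal variances and common correlation set out above.

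**What to change.** In Primary outcome measure and Economic evaluation, state the following.
- The control QALY is calculated at group level as 0.125·m0 + 0.25·m3 + 0.25·m6 + 0.125·m9 from confounder-adjusted cluster means. Adjustment may be by regression or by standardisation to the intervention group's case mix. Patient-level QALYs are used in the intervention group only.
- The control 9-month cost is taken from the 9-month cluster.
- The cost and QALY differences, the ICER, the plane and the acceptability curve all come from one bootstrap that resamples patients within each control cluster and whole patients in the intervention group. The planned 5000 replications can be kept.
- Seemingly unrelated regression is kept for 9-month effects paired with 9-month costs.

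In Handling missing data, state that time points never scheduled for a control are not imputed.

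The cost is rewording of these sections and bootstrap code, with no extra data. The downside is that the control cost-QALY correlation is captured only through the 9-month cluster, whose mean utility carries a weight of 0.125 in the QALY. The design allows no more than that.
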